## Abstract

**Background:**

Self-harm is common in the community with a lifetime prevalence of 13 %. It is associated with an elevated risk of overall mortality and suicide. People who harm themselves are high users of public services. Estimates of the 1-year risk of repetition vary between 5 and 15 % per year. Currently, limited evidence exists on the effectiveness of clinical interventions for young people who engage in self-harm. Recent reviews have failed to demonstrate any effect on reducing repetition of self-harm among adolescents receiving a range of treatment approaches. Family factors are particularly important risk factors associated with fatal and non-fatal self-harm among children and adolescents. Family therapy focuses on the relationships, roles and communication patterns between family members, but there have been relatively few studies of specifically family-focused interventions with this population. The Self-Harm Intervention: Family Therapy (SHIFT) Trial was funded by the National Institute for Health Research (NIHR) Health Technology Assessment programme (grant no. 07/33/01) following a commissioned call for this research.

**Methods/Design:**

SHIFT is a pragmatic, phase III, multicentre, individually randomised, controlled trial comparing Family Therapy (FT) with treatment as usual (TAU) for adolescents aged 11 to 17 who have engaged in at least two episodes of self-harm. Both therapeutic interventions were delivered within the National Health Service (NHS) Child and Adolescent Mental Health Services (CAMHS) in England. Participants and therapists were, of necessity, aware of treatment allocation, but the researchers were blind to the allocations to allow unbiased collection of follow-up data. Primary outcome data (repetition of self-harm leading to hospital attendance 18 months post-randomisation) were collected from the Health and Social Care Information Centre (HSCIC), augmented by directed searches of medical records at Acute Trusts. Secondary outcome data (including suicidal intent, depression, hopelessness and health economics) were collected at 12 and 18 months post-randomisation via researcher-participant interviews and by post at 3 and 6 months.

**Discussion:**

SHIFT will provide a well-powered evaluation of the clinical and cost effectiveness of Family Therapy for young people who have self-harmed on more than one occasion. The study will be reported in 2016, and the results will inform clinical practice thereafter.

**Trial registration:**

ISRCTN59793150. 26 January 2009.

## Background

The SHIFT Trial protocol was developed in response to a commissioned call for research. In accordance with the commissioning brief and in line with current UK clinical practice, self-harm is defined as any form of non-fatal self-poisoning or self-injury (such as cutting, taking an overdose, hanging, self-strangulation, jumping from a height, and running into traffic), regardless of motivation or the degree of intention to die. This definition includes what in the United States would be described as non-suicidal self-injury.

Self-harm is common in the community; a systematic review suggested a lifetime prevalence of self-harm of 13 % [1], whilst a recent meta-analysis reported an adjusted lifetime prevalence of non-suicidal self-injury of 17 % [2]. Self-harm is associated with an elevated risk of overall mortality [3–6] and suicide. In one follow-up study [7] of 15- to 24-year olds, who had presented to hospital following an episode of self-harm, the overall number of deaths from all causes was 3 % of cases, four times higher than expected. This was mainly due to an excess number of suicides (2 %), which were 10 times more frequent than expected. A recent multicentre study of those under 18 presenting following self-harm found that while mortality was relatively low at 0.9 % at a median follow-up period of 6 years, nearly half of these deaths were due to suicide [8]. Due to the young ages at which these deaths occur, the life years lost to the community due to suicide and the impact on family members are considerable.

Around 20–30,000 adolescents present to hospital each year having harmed themselves [9] although this represents only one in eight episodes of self-harm because the majority of young people who self-harm do not present to hospital [10]. Rates of self-harm amongst young people in the UK are not declining [11], and the epidemiology of self-harm appears to be shifting with dangerous methods such as hanging increasing in females [12], with higher rates among South Asian young women [13]. People who harm themselves are high users of public services [14], and increasing rates of self-harm will lead to an even greater demand for services.

In studies based on presentations to general hospitals in the UK, the majority of adolescents have harmed themselves by taking an overdose; self-poisoning with analgesics is particularly common [11, 15] and dangerous due to the risk of death from liver failure. At the community level, the most common methods of self-harm are cutting and overdose [10]. Young people have a poor understanding of the potential lethality of methods of self-harm, so interventions to prevent further episodes of self-harm is one approach to reducing both the morbidity and mortality associated with these acts.

Estimates of risk of 1-year repetition vary between 5 and 15 % per year [16], with 18 % in a recent UK multicentre monitoring study of over 5000 adolescents [11] and as much as 27 % in an average of 5 years of follow-up of around 4000 adolescents [8]. In addition, actual rates may be much higher if repetition that does not come to clinical attention is considered [9]. The risk of repetition is highest in the first year, but may remain high for many years after an episode [4, 17].

Currently, there is limited evidence about the effectiveness of clinical interventions for young people who engage in self-harm, although there has been much work in the area since the earliest systematic review [18]. Recent reviews have failed to demonstrate any effect on reducing repetition of self-harm among adolescents receiving a range of treatment approaches including therapeutic assessments and compliance enhancement in hospitals, youth-nominated support teams, tokens for hospital admission and home and family-focused interventions [19, 20]. The early promise of developmental group psychotherapy has not been replicated in larger studies [20]. Brent et al. [21] focused on aspects of trials that showed promise and concluded that interventions that activated family support, addressed motivations for change, were quickly mobilised (to reflect the elevated risk of repetition immediately post-episode) and promoted a positive affect are most likely to be able to demonstrate effectiveness. The heterogeneity of treatment as usual (TAU) and the lack of its characterisation of TAU [21], in addition to the many underpowered studies, have held back advances in this field.

Family factors are particularly important risk factors associated with fatal and non-fatal self-harm among children and adolescents [20, 22–25]. Difficulties in parent–child relationships, including those related to early attachment problems, and perceived low levels of parental caring and communication are related to increased risk of suicide and self-harm among children and adolescents [26]. A family history of self-harm is associated in adolescents with increased risk for suicide deaths [27–29] and for non-fatal self-harm [10, 30]. Parental mental illness and substance abuse are significant risk factors [16]. A strong association exists between self-harm and both childhood sexual abuse and physical abuse [31]. Young people who self-harm experience higher rates of exposure to recent stressful life events such as rejection, conflict or loss following the break-up of a relationship, conflicts and disciplinary or legal crises [15].

Systemic family therapy focuses on mobilising family resources and on the relationships, roles and communication patterns between family members. Surprisingly, there is only a small amount of literature on the use of family therapy with young people who self-harm [32–34], with most studies not powered to detect reductions in repeat self-harm. The SHIFT study seeks to evaluate the potential clinical and cost effectiveness of a family therapeutic intervention following adolescent self-harm.

## Methods/Design

### Design

SHIFT is a pragmatic, phase III, multicentre, individually randomised, controlled trial comparing Family Therapy (FT) with treatment as usual (TAU) for adolescents aged 11 to 17 who have engaged in at least two episodes of self-harm. An individually randomised design (Fig. 1) was chosen over a cluster randomised design as the risk of contamination between the two treatment arms was minimal: participants attended appointments at varying times and so could not cross compare, and family therapists were specifically instructed not to treat any participants in the TAU arm of the trial wherever possible.

**Fig. 1 Fig1:**
[figure not shown]
Trial design flow diagram

### Trial objectives and outcomes

The primary objective of the SHIFT trial is to assess the effectiveness of FT compared to TAU as measured by rates of repetition of self-harm leading to hospital attendance 18 months after randomisation. This primary outcome was selected because it is an objective measure of self-harm. This outcome can be quantified using routine hospital records data rather than relying on participant self-report and can be obtained even if contact has been lost with participants, thereby maximising the accuracy and completeness of the data collection.

Secondary objectives are to assess the following:The effectiveness of FT compared to TAU, measured by repetition rates of self-harm leading to hospital attendance at 12 months after randomisation.The cost per self-harm event avoided due to FT, measured using a structured health economics questionnaire designed by the trial health economist to be specific to this population.The characteristics of further episodes of self-harm (all episodes, not just those resulting in hospital attendance). This includes the number of subsequent self-harm events, time to next event, severity of event (fatal, near fatal or not) and dangerousness of the method used, as measured by the Suicide Attempt Self-Injury Interview (SASII) [35].Suicidal ideation in each trial arm, measured by the Beck Scale for Suicide Ideation [36].Quality of life in each arm, measured by the Paediatric quality of Life Enjoyment and Satisfaction measure (PQ-LES) [37] and parental completion of the General Health Questionnaire-12 (GHQ-12) [38].Depression in each arm, measured by the Children’s Depression Rating Scale – Revised (CDRS-R) [39].Overall mental health and emotional and behavioural difficulties in each arm via young person and parental completion of the Strengths and Difficulties Questionnaire (SDQ) [40].Hopelessness in each arm, via completion of the Hopelessness Scale for Children [41].Family functioning in each arm, measured by the McMaster Family Assessment Device [42] and the Family Questionnaire [43]. Mediator and moderator variables that influence engagement with and benefit from treatment (for example, number of sessions, medication use, referrals, mediators).Therapeutic alliance to family therapy, via family therapist, young person and parental completion of the System for Observing Family Therapy Alliances (SOFTA) [44]. Therapist adherence to the family therapy manual. A trial-specific approach has been developed for independent review of a representative sample of recorded FT sessions.

### Recruitment setting and participants

Young people and their primary caregivers were identified from 40 National Health Service (NHS) Child and Adolescent Mental Health Services (CAMHS) across three ‘hubs’ in England - Greater Manchester, London and Yorkshire. Following consultation with service users and clinicians, we elected not to screen young people at first presentation in the emergency department or primary care because in this time of crisis, immediately following the self-harm event, young people and their families would not be in a position to readily give fully informed consent. Young people were therefore screened for trial suitability at their first presentation to CAMHS following self-harm. They would thus have already been assessed by the emergency department staff, on-call CAMHS staff in hospital or by primary/community health staff before referral to CAMHS, where the screening took place. To be included in the trial, participants were required to meet the eligibility criteria described next.

### Inclusion criteria

Inclusion criteria included the following:Aged 11–17 years.Self-harmed prior to assessment by the CAMHS team (self-harm being the key feature of presentation).Engaged in at least one previous episode of self-harm (recorded by CAMHS or via self-report) prior to the index presentation.Where the presenting episode was due to alcohol or recreational drugs, the young person had explicitly stated that he / she was intending self-harm by use of these substances.The clinical intention was to offer CAMHS follow-up for self-harm.Lived with primary care-giver.Both young person and primary care-giver gave written informed consent, as appropriate.

### Exclusion criteria

Exclusion criteria include the following:At serious risk of suicide (clinical judgement);An ongoing child protection investigation within the family, which would have made treatment difficult to deliver;Would not have ordinarily been treated in generic CAMHS but rather by a specific service (for example, psychiatric inpatient care for severe major depressive disorder);Pregnant at time of trial entry;Actively being treated in CAMHS (as the possibility of randomisation might disrupt ongoing therapy);In a children’s home or short-term foster placement;Moderate to severe learning disability or lacked capacity to comply with trial requirements;Involved in another research project - at the time of trial entry or within the last six months;Sibling had been randomised to the SHIFT trial, or was receiving family therapy within CAMHS; orThe young person and one main care-giver had insufficient proficiency in English to contribute to the data collection.

All young people presenting to CAMHS following self-harm were screened. Data were recorded anonymously for those not meeting the above criteria in order to monitor trial uptake and representativeness of the trial population. Where a young person met the criteria, the assessing CAMHS clinician discussed trial participation at the assessment appointment, passed on the participant information sheets and requested consent for subsequent contact by a researcher. Those providing such consent were contacted by the researcher, who arranged to visit the family at home, obtained consent for participation in the trial and administered the baseline assessment.

### Recruitment, randomisation and blinding

Where the appropriate consent was obtained and baseline assessment completed, the researchers randomised participants sequentially via an automated system at the Clinical Trials Research Unit (CTRU) at the University of Leeds. Participants were randomly allocated on a 1:1 basis to receive FT or TAU, using a computer-generated minimisation programme incorporating a random element to ensure the treatment arms were well balanced for the following: centre (CAMHS team), gender, age (11 to 14 or 15 to 17), living arrangements (with parents or guardians/foster care), number of previous self-harm episodes (including index event) (2 or ≥ 3), and type of index episode (self-poisoning, self-injury, or combination). Where therapists were not aligned to a specific service but covered a number of services, additional randomisation of the lead therapist took place within the FT team in order to minimise case-selection bias.

Participants and therapists were, of necessity, aware of treatment allocation, but researchers were blind to the allocation to allow unbiased collection of follow-up data. CTRU was responsible for informing CAMHS clinicians and family therapists of randomisation outcome, to maintain researcher blinding.

### Data collection

Required data, assessment tools, collection time points and processes are summarised in Table 1.

**Table 1 Tab1:** Summary of assessments

Assessment (including who is involved)	Timeline (months post-randomisation)				
	Baseline	3	6	12	18
Eligibility and consent					
- Eligibility (assessed by clinician)	X				
- Consent (YP, P, R^a^)	X				
Background and demographics (YP, P, R - interview and case notes)					
- Personal details	X				
- Outline ‘index’ event details	X				
- Current co-morbid physical/mental health	X				
- Current psychotropic medications	X				
- History of abuse	X				
Follow-up data (collected from case notes)					
- Therapy details (provided by therapist)			X	X	
- Therapist supervision details (provided by therapist/supervisor)			X	X	
- Details of further self-harm episodes since consent (R)				X	X
- Psychotropic medication details (R)				X	X
- Referrals to other MH services (R)				X	X
- Re-referral to CAMHS (R)				X	X
- Admissions to hospital relating to mental health (R)				X	X
- All-cause mortality (CTRU to collect via MRIS flagging)					X
- Serious adverse event reporting and hospital attendance (R and HSCIC)	Ongoing collection				
Questionnaires (completed at researcher visit unless otherwise stated)					
- Family Questionnaire (P self-report, CTRU postal admin at 3 and 6 months)	X	X	X		
- System for Observing Family Therapy Alliances - SOFTA (completed by the family therapist and participants at Family Therapy session 3)		X			
- Suicide Attempt Self-Injury Interview - SASII (Interview with YP)	X			X	X
- Beck Scale for Suicide Ideation (YP self-report)	X			X	X
- Hopelessness Scale for Children (YP self-report)	X			X	X
- McMaster Family Assessment Device – FAD (YP and P self-report)	X			X	X
- General Health Questionnaire 12 – GHQ (P self-report)	X			X	X
- Strengths and Difficulties Questionnaire - SDQ (YP and P self-report)	X			X	X
- Children’s Depression Rating Scale – CDRS (Interview with YP)	X			X	X
- Paediatric Quality of Life Enjoyment and Satisfaction – PQ-LES (YP self-report)	X			X	X
- Inventory of Callous Unemotional Traits - ICU (YP self-report)	X				
- EQ-5D (YP self-report, CTRU postal admin at 6 months)	X		X	X	X
- Health Utilities Index 3 – HUI3 (P self-report, CTRU postal admin at 6 months)	X		X	X	X
- Health Economics questionnaire (YP and P self-report, CTRU postal admin at 3 and 6 months)	X	X	X	X	X

^a^YP, young person; P, parent/care-giver; R, researcher; HSCIC, NHS Health and Social Care Information Centre

### Baseline

At the baseline assessment, the researcher administered questionnaires to the young person, and self-reported questionnaires were also completed by the young person and the consenting primary caregiver.

### Follow-up

The primary outcome measure was obtained from Accident and Emergency Departments (A&E) and in-patient Hospital Episode Statistic (HES) data downloads from the NHS Health and Social Care Information Centre (HSCIC), which holds hospital attendance and admission data for hospitals across England. This method of primary outcome data collection was augmented by directed hospital record searches, undertaken by researchers at frequent intervals throughout the trial. Researchers searched Acute Trust records for episode details that were unclear from the central HES data, or for any hospital attendances for those participants who had not consented to the trial team providing their details to the HSCIC. Given that HES data sets are England-wide, this maximised collection of hospital attendance data, allowing for participants moving out of catchment area (within England). Collection of these routine data also minimised bias by eliminating the possibility of preferential researcher data collection at certain Acute Trusts.

Postal questionnaires were administered by CTRU at 3 and 6 months post-randomisation. If questionnaires were not returned, postal reminders were sent 2 weeks after the initial mailing and then again a further 2 weeks later.

Secondary outcome were obtained via face-to-face researcher interviews at 12 and 18 months following randomisation.

Data relating to treatment were provided by the treating CAMHS clinicians or Family Therapists, Clinical Studies Officers (CSOs) employed by the Research Networks in each locality and by the researchers, when blinding was no longer required (that is, after participant-reported follow-up data had been collected). The data included session attendance (FT and TAU), therapeutic approach (for TAU), referrals within and outside CAMHS, requirements for psychotropic medications, and liaison with other agencies. In addition, treating clinicians and participants completed the System for Observing Family Therapy Alliances scale (SOFTA) [44] at the end of the third treatment session. Supervision sessions for Family Therapists, and routinely provided clinical supervision for CAMHS clinicians were also recorded.

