
### Clinical service engagement

During the early stages of implementation of the trial CAMH Services were slow to engage with SHIFT. We deemed the slow initial recruitment a consequence of clinical unfamiliarity with research in many sites, the pressures of routine clinical practice and the sheer size of the task of involving so many clinicians in trial processes. The nature of the trial was such that anyone within the clinical team undertaking referral assessments could consider a young person’s eligibility for the trial and then be involved in TAU delivery. Ensuring all clinicians were fully informed about trial processes and had the research materials available was logistically complex. Very regular contact between the trial team and local services facilitated a collaborative and flexible approach, and was helped by the appointment of local trial ‘champions’ who took a lead in reminding their local colleagues of trial procedures. This process took the form of newsletters circulated by CTRU, posters for staff rooms and formal presentations delivered at research or team events. In addition, a training DVD was produced in which the Chief Investigator, researchers and trial therapists discussed the salient points of the trial in a short explanatory piece designed for clinicians.

Data collection from a large number of clinicians was not straightforward as there was little opportunity for learning on the clinicians’ part, a TAU clinician might only see one or two SHIFT participants over the duration of the trial so there is opportunity for missing data. Data collection (from clinicians) was thus a labour intensive task, and was ultimately superseded by data collection by researchers (where they could be un-blinded – for example, at the end of follow-up) and by Clinical Research Networks’ Clinical Studies Officers.

Despite the complexity of SHIFT, the trial ultimately recruited well, following implementation of intensive measures to improve screening and recruitment in 2010 after a slow start in 2009, and was able to complete recruitment at the end of 2013 following an extension award by HTA.

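### The rule for ending researcher blinding is tied to participant-reported data, so late extraction of hospital records for the primary endpoint is not covered by it

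*Protocol article*

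**What the plan says.** The article states the general principle under Recruitment, randomisation and blinding: participants and therapists know the allocation, but "researchers were blind to the allocation to allow unbiased collection of follow-up data". The abstract says the same.

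Two places say when that blinding may end:

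- **Follow-up.** Treatment data come from clinicians, family therapists, Clinical Studies Officers and also researchers, the last only "when blinding was no longer required (that is, after participant-reported follow-up data had been collected".
- **Clinical service engagement.** Collection from clinicians was replaced in part by collection by researchers "where they could be un-blinded – for example, at the end of follow-up".

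The same Follow-up section gives researchers a part in the primary outcome. The HES download is "augmented by directed hospital record searches, undertaken by researchers at frequent intervals throughout the trial". It describes two uses of these searches. The first is unclear records: "Researchers searched Acute Trust records for episode details that were unclear from the central HES data". The second is any attendance of a participant who did not consent to details being passed to the HSCIC.

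Table 1, under the heading "Follow-up data (collected from case notes", assigns further self-harm episodes, psychotropic medication, referrals, CAMHS re-referral and mental-health admissions to the researcher at months 12 and 18.

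**The concern.** In a trial that is open to participants and therapists, blind data collection is the main protection against observer bias. The article chose a record-based primary outcome because it is objective, and it claims unbiased collection. Yet the event that ends blinding is the completion of a different kind of data.

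Treatment data include session attendance and, for TAU, the therapeutic approach, so they reveal the arm. A researcher who has seen them and then searches hospital notes can be influenced in how hard to look and in what to record. For participants without HSCIC linkage this touches whether an attendance is found at all. For unclear HES records it touches the details on which the self-harm label depends. Either could move the primary hazard ratio, in a direction that cannot be known in advance.

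**Working it through.** The article gives no figure on this point, so the check is mainly a comparison of its statements.

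1. **What ends blinding.** Completion of participant-reported follow-up (Follow-up). By Table 1 the last such assessment is at 18 months.
2. **What the primary endpoint is.** Trial objectives and outcomes says it is taken from routine hospital records and not from self-report. Step 1 therefore does not wait for it.
3. **What researchers do for it.** They extract details for unclear HES episodes and find attendances for participants without HSCIC linkage (Follow-up).
4. **What unclear means.** Primary endpoint analysis shows that it includes not knowing whether an attendance was due to self-harm, and that some such cases may remain at analysis.
5. **Timing.** The endpoint window and the last interview both fall at 18 months. An attendance near the end of the window cannot be downloaded, queried and searched before it occurs, so some of this work may fall after the interview. The article gives no HES delivery lag, so how much is unknown.
6. **Other safeguards in the text.** The wording under Clinical service engagement refers to the end of follow-up, not to completion of hospital data. The planned sensitivity analysis addresses attendances whose details are still missing, not those already settled by someone who knew the arm. Nothing in the article keeps the searcher blind until a participant's attendances are final.
7. **Table 1 against Follow-up.** Follow-up lists referrals and psychotropic medication among the treatment data that researchers supply only once blinding has ended. Table 1 marks both for the researcher at month 12. The two agree if month 12 is the period described, and conflict if it is when the notes are opened.

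**Illustration on assumed inputs.** It shows only how the effect scales.

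- From the sample size section: 29% TAU event rate and 374 per arm. The conversion from rates to a hazard ratio reproduces the plan's own value: ln(1 − 0.29)/ln(1 − 0.188) = 1.645, against 1.64 stated.
- Assumed: no true effect; a share u of FT events settled by a researcher who knows the arm; a proportion b of those wrongly set to non-self-harm, in FT only.
- Observed FT rate p = 0.29 × (1 − u·b). Apparent HR (FT/TAU) = ln(1 − p)/ln(0.71). Events D = 374 × (0.29 + p). z = (√D/2) × |ln HR|. Chance of two-sided p < 0.05 = 1 − Φ(1.96 − z) + Φ(−1.96 − z).

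| u | b | p | HR | D | Chance of p < 0.05 |
|---|---|---|---|---|---|
| 5% | 50% | 0.283 | 0.97 | 214.2 | 5.6% |
| 10% | 50% | 0.276 | 0.94 | 211.5 | 7.3% |
| 20% | 50% | 0.261 | 0.88 | 206.1 | 14.5% |
| 20% | 100% | 0.232 | 0.77 | 195.2 | 44% |

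Only the product u·b matters. The effect is negligible if few events are settled late and material if many are.

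**The case against.** The strongest reply is that the exposure is narrow. Searches ran throughout the trial, and those made before the last interview were done while the rule kept researchers blind. Many attendances will be clear from HES. The primary model uses time to first event, so an ambiguous attendance after a clear one does not matter. Self-harm is defined regardless of motive or intent to die, which leaves less to judgement. All of this stands, and it limits the point to late searches and late queries.

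Three stronger readings are tempting, and the article does not support them.

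- **That researchers decide whether an attendance counts as self-harm.** The text says that they search for details. It does not name who makes the final classification, and an article may leave that to the full protocol.
- **That month-12 case-note work unblinds researchers before the 18-month CDRS-R and SASII interviews.** Follow-up places medication and referrals after blinding ends, and the Table 1 columns can be read as the period covered. CAMHS re-referral is not named in that section, but its list is not presented as complete. A breach is not established; only an ambiguity is.
- **That a size of bias can be quoted.** Any multiplier on the hazard ratio needs the share of attendances settled after unblinding and the difference in handling between arms. The article gives neither.

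The planned sensitivity analysis is a partial answer at most, for the reason given in step 6.

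**Conclusion.** The point holds in a limited form. As written, the rule ends researcher blinding at a milestone that does not include the primary endpoint, while researchers extract part of that endpoint. Hospital searches and queries worked after a participant's last interview may be done with knowledge of the arm, and the claim of blind, unbiased follow-up collection is not secured for them.

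This rests on two things: that the stated rule was applied as worded, and that some searches or queries were worked after the last interview. The first is the plain reading; the second is likely from the timing but is not stated. The size is unknown, and the table above is an assumed range, not an estimate for this trial. It is a fault in a stated rule and worth correcting; it is not evidence that the primary result is biased.

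**What to change.** Re-tie the rule to the primary endpoint. Anyone who extracts or classifies a participant's hospital attendances may see treatment data for that participant only after the 18-month interview is done and the 18-month hospital-attendance data for that participant are final. Until then, treatment data are collected by the Clinical Studies Officers or clinicians whom the article already uses for this.

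In Table 1, state for the month-12 researcher case-note rows whether month 12 is the period described or the time the notes are opened, and reconcile the answer with the Follow-up section. The rows need not be moved.

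The cost is that treatment data arrive later. A second reader from another hub is not needed, and under Research governance direct record access would require further Letters of Access. Trial status reports that follow-up is nearly complete, so the change would act mainly on searches and queries still open.
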